## Abstract

**Background:**

Refugees are exposed to various risk factors in shared accommodations in Germany where they are housed after their arrival. Due to their often traumatic experiences before, during, and after their flight and socio-structural post-migration stressors, refugees are potentially vulnerable to hazardous substance use. They form a structurally disadvantaged group for substance use prevention and intervention. Various barriers make it difficult for them to access the healthcare system and to get health information. Therefore, a participatory multi-component prevention concept for refugees in shared accommodations was developed. The aim of the trial is to evaluate the efficacy of this concept regarding the increase in knowledge about substance use among refugees living in shared accommodations.

**Methods:**

Based on a randomized controlled stepped-wedge design, the study will be conducted in a multicenter setting in nine shared accommodations and will aim to include refugees living in shared accommodations as well as social workers and psychologists working there.

**Discussion:**

This trial will be one of the first to generate evidence about effective participatory prevention concepts for refugees in shared accommodations. Evidence-based concepts for refugees can improve access to health care and might be helpful for the multidisciplinary workforce in shared accommodations.

**Trial registration:**

OSF Registry: osf.io/ebnj3. Registered on May 24, 2024. Registration DOI: https://doi.org/10.17605/OSF.IO/EBNJ3.

## Introduction

### Background and rationale {6a}

The UNHCRs Mid-year Trends Report [38] states that 110 million people are forcibly displaced within or outside their country of origin (UNHCR, [38]). As one of the three major hosting countries in the world, Germany hosted approximately 2.5 million people seeking international protection in mid-[12], who had to leave their home due to persecution, war, the consequences of climate change, dictatorships, poverty, and famine, with numbers increasing and expected to further increase over the years (UNHCR, [38]). Owing to their often traumatic experiences before, during, or after their flight, refugees are vulnerable to hazardous substance use and might use substances to cope with their psychological distress. The World Drug Report [40] highlights refugees as a vulnerable group for hazardous substance use due to their experiences of social and mental health issues in humanitarian settings and in their post-displacement environment (UNODC, [39]a; [40]b). In Germany, refugees are temporarily housed in shared accommodations. In these accommodation facilities, refugees are exposed to various socio-structural risk factors and post-migratory stressors [20, 41]. In addition, refugees face various barriers to existing substance use interventions and to adequate information about induced health risks [23, 28, 31, 42, 44]. Therefore, there is a need for culturally sensitive and low-threshold prevention measures that give health-related information, reduce the need for intervention, and can be applied at an earlier stage during individuals’ stay in shared accommodations.

While much is known about forced migration on the one hand and substance abuse on the other hand, little is known about hazardous substance use among refugees. There is some evidence about the epidemiology of substance use among refugee populations [15, 17, 44] and about substance use prevention among refugees (summarized by [19], however, there is no evidence about effective evidence-based concepts to prevent substance use among refugees in the setting of shared accommodations. The existing findings from other target groups are only partially transferable to this specific group of refugees and their living environment [18], which is characterized by sharing rooms, lack of privacy, limited space, and the cohabitation of many different people from different countries, cultures, and religions.

Specific, culturally sensitive, adequate, and evidence-based prevention concepts containing access to information are urgently needed but have not yet been developed and evaluated. Therefore, the aim of this trial is to evaluate the effects of a multi-component prevention concept for refugees in shared accommodations in Germany, which has been developed in a participatory way with refugees, social workers, and researchers.

### Objectives {7}

The primary objective of this study is to evaluate the efficacy of a multi-component prevention concept for refugees in shared accommodations regarding refugees’ knowledge about hazardous substance use and induced health risks. It is hypothesized that their knowledge about the health system, addiction counselling, risks of hazardous substance use, and access to supportive structures increases in shared accommodations where the concept is implemented (intervention group) in comparison to the shared accommodations where the concept is not yet implemented (control group). The secondary objectives are to measure the impact of concept implementation on health literacy, attitudes towards substance use, hazardous substance use, depression, anxiety, and stress as well as the knowledge of the workforce about hazardous substance use and induced health risks.

### Trial design {8}

The study is based on a randomized controlled stepped-wedge design and will be conducted in a multicenter setting in nine shared accommodations. The stepped-wedge design ensures that the prevention concept is available to all refugees in the nine shared accommodations in the final phase of the study. In addition, the design enables a deeper analysis of the effect over time, which a conventional cluster randomization would not offer. Randomization is planned for the allocation of the shared accommodation to the intended clusters A, B, and C in three steps (step 1: intervention in cluster A; step 2: intervention in clusters A and B; and step 3: intervention in clusters A, B, and C).

## Methods: participants, interventions, and outcomes

### Study setting {9}

The study will take place in nine shared accommodations in Stuttgart, Germany. The survey will consist of three clusters with three accommodations each. Using the web-based randomizing program random.org, shared accommodations are randomly assigned to each cluster. Implementation takes place in cluster A in weeks 1–3, cluster B in weeks 4–6, and cluster C in weeks 7–9. This results in five survey times t_0_–t_4_ (see Table 1): baseline, after implementation in clusters A, B, and C as well as the follow-up. In the study, data is collected and evaluated both at the level of the refugees and at the level of the qualification of the setting (qualification of the professionals in the shared accommodation, structural conditions of the setting). Qualified social workers or psychologists perform the implementation of the prevention concept.

**Table 1 Tab1:**
[figure not shown]
Trial design

### Eligibility criteria {10}

Inclusion criteria for the participants are (1) being a refugee or asylum seeker or workforce in shared accommodations; (2) residing or working in selected shared accommodations; (3) being 18 + years, and (4) language proficiency (oral/written) in the languages in which the survey instrument is available (Arabic, Turkish, Farsi, Russian, French, German, and English). Exclusion criteria are (1) persons in acute mental health crises (e.g., suicidality, psychosis) and (2) minors.

The inclusion criteria (1), (2), (3), and (4) are tested by members of the organizational support groups before inviting participants to the trial. Members of the organizational support groups know the residents of shared accommodations very well by providing them day-to-day support and social services. They also have access to all relevant medical and organizational files. Assessment of exclusion criterion (1) (acute mental health crisis) is also performed by members of the organizational support groups by behavioral observation in the shared accommodations on a daily basis. Values of 30 or lower on the Global Assessment of Functioning Scale [1], of the DSM-IV are considered to be indicators of acute mental health crises. To our knowledge, no formal measures for objectivity, reliability, and validity of the GAF for residents of shared accommodations for refugees are available; however, it is assumed that day-to-day interaction of staff and refugees is perfectly suited to detect serious impairment as described above. Apart from the nine included shared accommodations, there are specific shared accommodation facilities in which only refugees with diagnosed acute mental crises and mental illness are housed. These so-called protective facilities are deliberately excluded from the sampling to ensure the safety of the participants. As a result, it is initially unlikely that a person with a diagnosed mental illness will be invited to participate in the study. Exclusion criterion (2) (age below 18) is also rated by members of the organizational support groups based on organizational files.

### Who will take informed consent? {26a}

The research team on site and the organizational support groups provide information and flyers about the purpose of the study and how to participate in different languages (Arabic, Turkish, Farsi, Ukrainian, Russian, French, German, and English). If they meet the eligibility criteria and are willing to participate, participants can give written consent and agree to the use of their data. Formal informed consent is given before starting to fill in the questionnaire online.

### Additional consent provisions for collection and use of participant data and biological specimens {26b}

This is not applicable because no biological specimens will be collected in this trial.

## Interventions

### Explanation for the choice of comparators {6b}

The comparators are shared accommodations, in which the intervention was not yet implemented according to the stepped-wedge design. Shared accommodations that are waiting for the intervention will not be offered any additional interventions.

### Intervention description {11a}

To address refugees as a particularly vulnerable group for hazardous substance use, the research and development project “PraeWi” (funded by the German Federal Ministry of Education and Research) developed a participatory multi-component prevention concept containing different addiction prevention measures for the workforce and for refugees working or living in shared accommodations (see Table 2).

**Table 2 Tab2:** Multi-component prevention concept

Components	Prevention measures
1. Health communication through peers	Information videos
	Peer education
2. Tools for the workforce	Guide with situational recommendations
	E-learning-tool for the workforce
3. Bridges in support system	Linking the specialist areas Flight—Trauma—Addiction
4. Online prevention	Podcast
	BePrepared-App
5. Target group-specific information and communication strategy	Communicating the project results to different population groups/stakeholders in a tailored target group approach

This concept provides cultural sensitive information videos in different languages (Arabic, Turkish, Farsi, Ukrainian, Russian, French, German, and English), a podcast, an app and material for peer education workshops for refugees, and an e-learning tool and guidelines for the workforce of shared accommodations. The prevention measures of components 1–4 will be provided via QR codes that give access to the project website where all the material can be downloaded. The psycho- and socio-educative materials include information about the health system, addiction counselling, risks of hazardous substance use, and access to supportive structures. Component 5 is a superordinate component and therefore not part of the intervention.

The concept is based on an acceptance-oriented perspective to promote risk awareness and competence as well as health literacy [2, 11, 14, 43]. It was developed in a participatory way. Moreover, the study will be conducted with refugees participating in the research and implementation team.

Since the intervention is targeting several shared accommodations (each with a number of refugees), adherence to protocol is not assessed on an individual level. However, on the level of each shared accommodation, adherence will be checked by the project management group by making sure that all prevention materials are available in the study centers. As the intervention material consists of 4 prevention components that are made available at each study center (component 5 is of a more global nature), adherence scores rated by members of the project management group can range from 0 (no materials available) to 4 (all 4 materials available).

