### Recruitment {15}

Shared accommodations are selected where there is a balanced resident structure in terms of country of origin, age, gender distribution, and family situation. Attention is also paid to the inclusion of different sizes and forms of housing (e.g., system construction, existing buildings, etc.). The sample will be drawn using the respondent driven sampling (RDS) method, a further development of snowball sampling, and like this is suitable for populations that are hard to reach [7, 30, 35, 36] for the researchers but whose members are well networked and enables weighting in the analysis through better control of the recruitment channels in order to ensure representativeness of the sample. Participants are invited to take part in the trial by the organizational support groups and with multilingual information material (the following languages are available: Arabic, Turkish, Farsi, Ukrainian, Russian, French, German, and English). During the conduct of the trial, the organizational support groups will make sure that participants continue in the trial by regularly reminding them to participate.

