### Implementation {16c}

The implementation of the prevention concept will be carried out by a multidisciplinary team of professionals, including researchers of the study team, social workers, and psychologists as well as refugees living in shared accommodations. Staff and peer training will be conducted beforehand to ensure consistent and standardized implementation. The implementation of the prevention concept is developed in close collaboration with residents of shared accommodations to ensure high acceptance and effectiveness.

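### As described, nothing stops waiting accommodations from using the web-delivered materials before their step, and nothing would show whether they did

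*Protocol article*

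**What the plan says.** **Delivery.** Under Intervention description {11a}, components 1–4 are "provided via QR codes that give access to the project website where all the material can be downloaded". These components include the videos, peer-education material, podcast, app, staff guide and e-learning tool. Component 5 is not part of the tested intervention.

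**Place and timing.** Study setting {9}: "The study will take place in nine shared accommodations in Stuttgart, Germany". The roll-out is: "Implementation takes place in cluster A in weeks 1–3, cluster B in weeks 4–6, and cluster C in weeks 7–9". Cluster B therefore waits three weeks, and cluster C six weeks, while the material is in use elsewhere in the city.

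**Control condition.** Explanation for the choice of comparators {6b}: "Shared accommodations that are waiting for the intervention will not be offered any additional interventions".

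**Measurement of use.** Under {11a}, "adherence to protocol is not assessed on an individual level". What is recorded is a score from 0 to 4 per accommodation, counting how many of the four components are available there.

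**Training.** Implementation {16c}: "Staff and peer training will be conducted beforehand to ensure consistent and standardized implementation". The implementing team includes "social workers, and psychologists as well as refugees living in shared accommodations".

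**Sampling.** Recruitment {15} chooses respondent-driven sampling as suited to populations "whose members are well networked".

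**The concern.** The primary contrast is between accommodations that have the concept and those still waiting for it. A QR code or web address is easily passed on, and the article describes no gate tied to an accommodation's step. The comparator statement says what waiting sites will be offered. It does not stop a resident or staff member from receiving a link from someone in cluster A.

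The measurement choice makes this worse. The availability score checks that materials are present, and no check is described that they are absent or unused at waiting sites. Without individual exposure data, neither the intention-to-treat nor the per-protocol analysis in {20c} could reveal leakage. At t0 no accommodation has the concept and at t3 all have it, so concurrent comparisons of treated and waiting accommodations exist only at t1 (A against B and C) and t2 (A and B against C). That is when leakage would occur. A null result could then mean an ineffective concept or a diluted contrast, and the data would not separate the two.

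**Working it through.** **Inputs from the protocol article.** Nine accommodations in three sequences of three; primary outcome at t0–t3 ({12}); mean difference 0.15, ICC 0.01, power 0.80, significance level 0.05, n = 252 or 28 per accommodation ({14}). The standard deviation (SD), the individual autocorrelation (IAC) and the sidedness of the test are not given. A two-sided test is assumed.

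**Step 1: the plan's own figure.** With those inputs missing, 252 can be neither confirmed nor refuted. A closed-cohort stepped-wedge mixed model with fixed period effects, four periods and an assumed SD of 1 gives, at 28 per accommodation:

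| Assumed IAC | Power |
|---|---|
| 0 | 30% |
| 0.5 | 46% |
| 0.7 | 65% |
| 0.79 | 80% |

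Other pairs also reach 80%, such as an SD of about 0.84 with an IAC of 0.7. The dilution check below therefore takes the stated 80% as given and does not rest on any of these values.

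**Step 2: what leakage does to the estimate.** Let X be 1 if an accommodation has reached its step at a survey and 0 otherwise. Let waiting accommodations gain a fraction c of the full effect at t1 and t2. The effect actually received, in units of the full effect, is then

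- t0: 0 everywhere (X = 0)
- t1 and t2: X + c(1 − X) = c + (1 − c)X
- t3: 1 everywhere (X = 1), which also equals c + (1 − c)X

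From t1 onward c is a constant common to all accommodations, so the period effects absorb it and the treatment coefficient is (1 − c) times the true effect. This holds at any ICC or IAC. A numerical refit at IAC 0 and 0.72 returned 0.9, 0.8 and 0.7 for c = 0.1, 0.2 and 0.3. The factor is exact only for leakage that is uniform across the waiting cells.

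**Step 3: power.** At 80% power the effect divided by its standard error is 1.960 + 0.842 = 2.802. With dilution, power = Φ(2.802(1 − c) − 1.960). The sample size that would offset it is approximately 252/(1 − c)².

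| Assumed c | Estimated difference | Power | Approx. N to restore 80% |
|---|---|---|---|
| 0 | 0.150 | 80% | 252 |
| 0.05 | 0.1425 | 76% | 280 |
| 0.10 | 0.135 | 71% | 312 |
| 0.20 | 0.120 | 61% | 394 |
| 0.30 | 0.105 | 50% | 515 |

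**Step 4: what c means.** It is a fraction of the effect, not a share of people exposed. It is roughly the share exposed times the part of the full effect that exposed people gain. For example, if 40% of waiting residents were exposed and gained half the effect, c = 0.40 × 0.50 = 0.20. Both figures in this example are assumptions.

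**The case against.** The strongest reply is that this is an inference from a condensed article. It does not say that the codes are the same at every site, that the website is public, or that all content is live for everyone once cluster A starts. Roll-out is described as stepwise, and access control could stand in a fuller protocol. This is fair. A reader might infer that an open site serves all nine accommodations from step 1, but the text does not support that.

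The training sentence is equally open. A reader might infer that staff and peers at all sites are trained before roll-out. Training before each site's own step is just as natural a reading, and Concealment mechanism {16b} releases allocation only after baseline. Any early effect on workforce knowledge also depends on which section governs: {12} places that outcome nine weeks after first implementation, while {13} lists short-term outcomes at t1–t3.

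The sampling remark describes communities and does not say that ties run between these nine accommodations. Nor is a forwarded link the whole intervention, which also includes peer education, links between specialist services and encouragement on site. Partial exposure would dilute less than full exposure.

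What remains is enough for the point. Delivery through a project website and adherence scored by availability alone are stated choices, and nothing described alongside them would limit or reveal early use.

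**Conclusion.** The point stands as an unguarded and undetectable risk to the primary contrast, worth a low-cost change. It does not show that contamination will occur, and the documents give no basis for estimating how much.

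Uniform leakage of a fraction c leaves (1 − c) × 0.15. Across c = 0.10 to 0.30, power falls from the stated 80% to between about 71% and 50%. This assumes a two-sided test, a constant effect once an accommodation reaches its step, equal leakage in all waiting cells at t1–t2, and that the stated 80% is correct. A reader might treat an IAC of about 0.79 as the plan's own basis for 80% power. It is not: that value is back-calculated with an assumed SD of 1. The missing SD and IAC are a separate matter. The training element counts only if training at all sites before roll-out is what is meant.

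**What to change.** 1. Give each accommodation its own QR links or access codes, activated at the start of its step, and keep the material off openly accessible pages until t3 is complete.
2. Log access per link or code. Logs show when and through which accommodation's link the material was opened, but not who opened it.
3. Because a link active in cluster A can still be forwarded, add one short item to the t1–t3 surveys asking whether the participant has seen or used the materials. Report exposure in untreated periods by accommodation and survey.
4. Keep the intention-to-treat analysis by randomised step as primary. Add a sensitivity analysis for exposure in untreated periods, for instance the estimate over a range of c informed by the logs and the survey item. Simply dropping exposed participants would select on behaviour after randomisation.
5. State what *beforehand* means for training. If it means all sites before roll-out, tie staff and peer training to each sequence's own step, after the survey that closes the preceding one: A after t0, B after t1, C after t2.

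**Cost.** Website configuration, nine sets of codes, one extra survey item and public release delayed until after t3; three training rounds only if item 5 applies. The design and each accommodation's access at its own step are unchanged. Trial status gives version 2 as 08/2024 and the end of data collection as 10/2024. If the steps have already run, what remains is to report how access and training were handled, any website logs that exist, and the sensitivity range.

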### Criteria for discontinuing or modifying allocated interventions {11b}

Participants are free to use or not use the prevention measures. In case of serious adverse events, the installed psychological background service will be consulted and the project steering committee will decide whether the study should be discontinued. As the focus of the concept is prevention, no worsening of diseases will be expected.

